The investigator assessing the primary and secondary outcomes will be blinded to the groups. The number of patients reporting subjective symptoms of inferior alveolar nerve injury after surgery will be considered as the primary outcome. The secondary outcome will include the number of patients experiencing signs and symptoms of nerve injury that are confirmed by an abnormal clinical neurosensory test. It will also include those patients having symptoms of injury lasting more than six months post-surgery. First, the patients will be enquired about abnormal sensations in the ipsilateral lip and chin and compared to the contralateral side. This will be confirmed by standard clinical quantitative nerve testing procedures such as static light touch, two-point discrimination, brush-directional discrimination, and pin pressure nociception [21]. Patients with altered sensation will be examined at day one, day seven, day 30, day 60, day 90, and then day 180 postoperatively to assess their recovery pattern. If needed, further consultations will be taken for persistent paresthesia/anesthesia.

Training and calibration of personnel

Trained oral and maxillofacial surgeons will carry out the assessment independently. They will be experienced in the identification and diagnosis of maxillofacial structures utilizing both OPG and CBCT. They will be blinded by the clinical outcome. All three planes will be assessed through the implant planning screen and multiplanar reconstruction screen.

Mitigation of confounders

There can be various confounders in this study. First of all, the patients will be randomized to the two groups based on a random computer generator sequence to avoid selection bias. Group allocation will be done by contacting the principal investigator for randomization. Experienced surgeons will be carrying out the procedure, and their experience will be noted down. Besides, it will be performed by different surgeons for external validation. The type of impaction will be noted to assess difficulty. The technique of surgical removal will be standard, involving odontectomy. The evaluator of the outcome will be blinded to the group of study participants.

Sample size calculation

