Hypotheses will be tested using the one-tailed superiority analysis method, with 80% power and a 5% level of significance, based on the incidence of patient-reported abnormal sensations after surgery. Considering a superiority margin of 33% as per reference values between the incidence of temporary inferior dental nerve paresthesia of 25% in the OPG group and 58% in the CBCT group, the total sample size will be 68 (34 in each group) using the following formula [18].

 \begin{document}p=(p_1+rp_2)/(1+r )\end{document}

\begin{document}n ≥ [Z_(1-α/2) √((r+1)p(1-p) )+Z_(1-β) √(rp_1 (1-p_1 )+p_2 (1-p_2 ) )]^2/(r (p_2-p_1 )^2 )\end{document}

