## Results

The results will be described based on Standards for Reporting of Diagnostic Accuracy (STARD) guidelines. The statistical analyses will be done with the ‘intention to treat’ principle. The complete dataset analysis will encompass all study participants, based on the mentioned inclusion/exclusion criteria, who have no missing data for any of the parameters in the dataset. The primary outcome will include the number of patients experiencing inferior dental nerve injury as evidenced by the subjective presence of paresthesia, anesthesia, or dysesthesia after mandibular third molar surgery. Secondary outcomes will include the number of patients with nerve injury confirmed by abnormal clinical neurosensory testing and nerve injury lasting for more than six months.

Baseline characteristics will be used to describe data. Mean and standard deviation will be used to describe continuous variables. Frequencies and percentages will be used to describe categorical data. The outcome variables for continuous data, if normally distributed, will be summarized by using the mean, range, standard error, standard deviation, and confidence interval at 95%. The outcome variables for continuous data will be analyzed using an independent sample t test at the 5% level of significance (P<=0.05) assuming a normal distribution.

Data not following normal distribution will be described by nonparametric tests using mean, median, lower, and upper quartiles. A Mann-Whitney test will be used for testing such significance. Chi square analysis will be utilized to analyze efficacy for the categorical variables. Fisher exact or chi-square test will be used to analyze nominal and dichotomous data. Analysis for logistic regression will be done to recognize possible risk factors for impairment of the inferior alveolar nerve. Comparative groups will be analyzed by a t test at the 5% level of significance (P<=0.05). Sensitivity and specificity of CBCT and OPG in prediction of nerve injury will be confirmed on the basis of results obtained on subjective/objective nerve testing after surgical removal of a tooth (Table 1).

**Table 1 TAB1:** Master chart format for recording various study variables

	Demographic variables									Pathological variables			OPG findings							Cone beam computed tomography					Surgical variables							outcome variables													

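### The 68 patients are the number that must be analysed, with no allowance for loss, and whether 80% power survives missing data depends on a sidedness and a test that the article leaves unsettled.

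*Protocol article*

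**What the plan says.** Under Sample size calculation, the protocol article sets the test and the error rates: "Hypotheses will be tested using the one-tailed superiority analysis method, with 80% power and a 5% level of significance". The planning rates are "temporary inferior dental nerve paresthesia of 25% in the OPG group and 58% in the CBCT group", and the result is that "the total sample size will be 68 (34 in each group) using the following formula [18". The formula printed below that sentence uses the critical value Z(1-α/2) and has no term for loss. The section mentions no allowance for patients who drop out.

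Under Results, two statements on who is analysed stand next to each other. The first is "The statistical analyses will be done with the ‘intention to treat’ principle". The second describes a complete dataset analysis of participants "who have no missing data for any of the parameters in the dataset". The section also offers Fisher's exact test or chi-square for dichotomous data, without giving the sidedness.

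On outcomes and follow-up, the Patient screening process section says: "The number of patients reporting subjective symptoms of inferior alveolar nerve injury after surgery will be considered as the primary outcome". Patients with altered sensation are then seen at "day one, day seven, day 30, day 60, day 90, and then day 180 postoperatively to assess their recovery pattern". Table 1 has subjective and objective nerve-injury columns at six times from day 1 to 6 months, besides many demographic, imaging and surgical fields.

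**The concern.** A sample size that equals the bare formula result is the number needed in the analysis, not the number to recruit. Patients are randomised before surgery, so some may never be operated on. The complete-data sentence could remove others for a blank field or a missed late visit, even though their early symptom report is in hand. If that sentence governs the primary comparison, fewer than 34 per group would be analysed, and the stated 80% would no longer be the power of the analysis that is run.

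Two things are at stake. One is whether the power statement can be relied on. The other is whether patients with a recorded primary outcome are discarded for reasons unrelated to it, which lowers power and invites attrition bias.

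**Working it through.** **Inputs.** From Sample size calculation: p1 = 0.25 (OPG), p2 = 0.58 (CBCT), power 80%, significance level 5%. Allocation is equal (34 in each group), so r = 1. The loss rate is not given; 10% to 20% is an assumption.

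**Reproducing the plan's figure.** The pooled rate is p = (0.25 + 0.58)/2 = 0.415. Write

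- A = √(2 × 0.415 × 0.585) = 0.6968
- B = √(0.25 × 0.75 + 0.58 × 0.42) = √0.4311 = 0.6566

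Then n = (zα·A + 0.8416·B)² / 0.33².

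- With zα = 1.960, as printed: (1.3657 + 0.5526)² / 0.1089 = 33.79, rounded up to 34 per group (68 in total). This is the plan's figure exactly.
- With zα = 1.645, as the one-tailed text implies: (1.1462 + 0.5526)² / 0.1089 = 26.50, rounded up to 27 per group (54 in total).

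So 68 comes from the two-sided critical value and nothing has been added for loss. Measured against the one-tailed text, the same 34 leaves 7 per group to spare, by accident of the critical value rather than by a stated allowance.

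**Power after loss.** Formula power is Φ[(0.33·√n − zα·A)/B]. For n = 34 two-sided this is Φ[(1.9242 − 1.3657)/0.6566] = Φ(0.851) = 80.3%. Exact power is found by summing the binomial probabilities of all tables that the test rejects. The numbers left per group are 34 × 0.9 = 30.6, taken as 31, and 34 × 0.8 = 27.2, taken as 27.

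| Analysed per group | Assumed loss | Formula, two-sided | Formula, one-sided | Exact chi-square, two-sided | Exact chi-square, one-sided | Exact Fisher, one-sided |
|---|---|---|---|---|---|---|
| 34 | none | 80.3% | 88.2% | 80.9% | 89.1% | 83.5% |
| 31 | about 10% | 76.4% | 85.4% | 77.6% | 84.9% | 78.0% |
| 27 | about 20% | 70.2% | 80.7% | 69.2% | 81.2% | 73.6% |

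Two-sided Fisher has 73.9% power with no loss at all.

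**Where 80% is crossed.** Two-sided by the formula, it is crossed at once: 79.0% at 33 per group. One-sided by the formula, it is crossed at 26 per group (79.3%), that is, beyond about 22% loss. With one-sided Fisher, power is just under 80% at 32 per group, which is about 6% loss (2/34). Of the four combinations of test and sidedness that the article leaves open, only one-sided chi-square stays above 80% through 20% loss.

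The one-sided figures take the rejection region to lie towards a higher rate in the CBCT group, because that is where the plan puts the 58%. Whether that direction is intended is a separate question.

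**The case against.** A reader might infer that the design simply fails to deliver 80% power at its own rates. The documents do not support that. The text declares a one-tailed test at 5%, and on that test with chi-square the power is 88% with nobody lost and still about 81% at 27 per group. That stands, and it rules out a flat statement that the power is about 70% to 76%.

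A reader might also infer that 80% holds only if all 68 patients are operated on and attend every visit. That too goes too far. Even two-sided, exact chi-square power at 33 per group is 81.7%, slightly above the 80.9% at 34, because exact power moves unevenly with n.

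The route by which loss reaches the primary comparison is less certain than it first looks:

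- The day-180 schedule is stated for patients with altered sensation, not for everyone.
- Subjective symptoms are recorded from day 1, so the primary outcome may be known long before a late visit is missed.
- Intention to treat is named immediately before the complete-data sentence.
- Taken with full literalness, that sentence would exclude the whole OPG group, whose CBCT columns in Table 1 are blank by design, so it can hardly be meant in its strictest form.

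Finally, no loss rate is given, and a full protocol might hold a recruitment allowance.

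What remains is this. The article itself fixes the total at 68, and that total equals the uninflated result. The one-tailed cushion is a by-product of two conflicting statements, not a planned reserve, and it disappears under Fisher's test. The complete-data sentence is in the text, and nothing says that it does not govern the primary comparison.

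**Conclusion.** The point holds in a limited form. The 34 per group is the bare result of the two-sided formula (33.79), so 68 is the number to be analysed. The article pairs it with a rule that can drop patients for any blank field, and does not reconcile that rule with intention to treat.

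The consequence for power is conditional. At 25% v 58% and an assumed 10% to 20% loss, it ranges from a clear shortfall (about 76% to 70%, two-sided formula), through a moderate one (about 78% to 74%, one-sided Fisher), to none (about 85% to 81%, one-sided formula). The finding is therefore that 80% power is not assured, not that it is missed. It rests on the plan's own event rates and on a loss rate that the documents do not supply. The 68 is not an arithmetical error in the printed formula.

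**What to change.** 1. Run the primary comparison on every randomised patient who has the early post-operative symptom report, in the group assigned. A missed later visit or an unrelated blank field then does not remove a patient. If a complete-data analysis is kept, label it as supplementary and say which fields it requires.
2. State that 68 is the number to be analysed. Patients who are randomised but never operated on, or who give no early report, would still reduce it, so a loss assumption is needed even after step 1.
3. Reconcile the one-tailed text with the Z(1-α/2) in the formula, and name one test for the primary outcome.
4. Restate the power for that sidedness and test, with no loss and under the assumed loss.

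The cost is a few sentences under Sample size calculation and Results. The stated power may become less favourable, depending on the choice in step 3. No extra patients are needed.

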## Results

The results will be described based on Standards for Reporting of Diagnostic Accuracy (STARD) guidelines. The statistical analyses will be done with the ‘intention to treat’ principle. The complete dataset analysis will encompass all study participants, based on the mentioned inclusion/exclusion criteria, who have no missing data for any of the parameters in the dataset. The primary outcome will include the number of patients experiencing inferior dental nerve injury as evidenced by the subjective presence of paresthesia, anesthesia, or dysesthesia after mandibular third molar surgery. Secondary outcomes will include the number of patients with nerve injury confirmed by abnormal clinical neurosensory testing and nerve injury lasting for more than six months.

Baseline characteristics will be used to describe data. Mean and standard deviation will be used to describe continuous variables. Frequencies and percentages will be used to describe categorical data. The outcome variables for continuous data, if normally distributed, will be summarized by using the mean, range, standard error, standard deviation, and confidence interval at 95%. The outcome variables for continuous data will be analyzed using an independent sample t test at the 5% level of significance (P<=0.05) assuming a normal distribution.

Data not following normal distribution will be described by nonparametric tests using mean, median, lower, and upper quartiles. A Mann-Whitney test will be used for testing such significance. Chi square analysis will be utilized to analyze efficacy for the categorical variables. Fisher exact or chi-square test will be used to analyze nominal and dichotomous data. Analysis for logistic regression will be done to recognize possible risk factors for impairment of the inferior alveolar nerve. Comparative groups will be analyzed by a t test at the 5% level of significance (P<=0.05). Sensitivity and specificity of CBCT and OPG in prediction of nerve injury will be confirmed on the basis of results obtained on subjective/objective nerve testing after surgical removal of a tooth (Table 1).

**Table 1 TAB1:** Master chart format for recording various study variables

	Demographic variables									Pathological variables			OPG findings							Cone beam computed tomography					Surgical variables							outcome variables													
Patient	Age	Sex	ASA class	Medical co-morbidity	Smoking (frequency)	Alcohol (frequency)	Oral contraceptive use (Y/N)	Oral hygiene (good, moderate. Poor)	Side (38/48)	Pericoronitis (Y/N)	Pocket >4mm(Y/N)	Caries(Y/)	Angulation	Depth of impaction (A, B,C)	Ramus overlap (I, II,III)	Difficulty index	Length of red line (in mm)	Rood Shehab criteria (name/s)	Vertical over projection of root with inf alv canal Class 1,2,3,>3	Inf alv canal position in relation to root (inf, ling, buccal, inter-radicular)	Distance between root and IA canal vertically and buccolingually	Root in contact with IA canal (Y/N)	Cortical layer of canal (present/absent)	Shape of canal (round/oval/narrowing)	Experience of surgeon (<100 M3 removed, 101-500 M3 removed, 501-1000 M3 removed, 1001-3000 M3 removed, >3000 M3 removed)	Incision/flap (envelope/triangular/quadrilateral)	Bone removal (Y/N)	Odontectomy (Y/N)	No.of roots (1,2,>2)	Inf alv nerve visible (Y/N)	Intra-operative hemorrhage from IA canal	Subjective inf alv nerve injury (Y/N)						objective inf alv nerve injury (Y/N)						infection	any other complication
																																Day 1	Day 7	1 month	2 months	3 months	6 months	Day 1	Day 7	1 month	2 months	3 months	6 months		
1																																													
2																																													
3																																													
4																																													
5																																													
6																																													
7																																													
8																																													
9																																													
10																																													

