In the OPG group, the patients will be subjected to digital OPG alone (Planmeca Promax-Planmeca, Helsinki, Finland). In the CBCT group, a high-resolution CBCT scan will be done for the mandible preoperatively in addition to baseline OPG (Planmeca Promax 3D - Planmeca, Helsinki, Finland). CBCT/OPG images will be assessed by experienced surgeons. They will decide their surgical steps based on information from the OPG/CBCT images. All lower wisdom teeth will be removed using local anesthesia by standard surgical protocol with odontectomy. Variables, including the operating surgeon’s experience, will be noted down along with the outcome variables of subjective and objective nerve injury from day one till six months after surgery. The CONSORT flow diagram showing the progress of the study is outlined in Figure 1.

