**Figure 1 FIG1:**
[figure not shown]
CONSORT flow diagram [19]

Reference standard and its rationale

Orthopantomogram (OPG) is established diagnostic equipment that is used to assess the lower wisdom teeth and their relationship with the inferior dental nerve canal before surgery [10]. Due to challenges associated with the placement of the intraoral receptor during periapical radiography, for evaluating mandibular third molars, it is recommended to employ OPG as a primary imaging modality prior to surgical extraction. OPG is advantageous, as it can be conducted with minimal patient discomfort compared to intraoral techniques. Additionally, it is a low-radiation method that captures all wisdom teeth in a single film, equivalent to approximately two to 16 intraoral film exposures.

Patient screening process

In the assessment of OPG, the initial step involves determining if there is observance of one or more of Rood and Shehab’s criteria indicating close approximation between the root of the third molar and inferior alveolar canal. This will be the eligibility criteria for patient recruitment. All these patients will be assigned to either the OPG group or the CBCT group by random computer-generated sequence. Group allocation will be done by contacting the principal investigator for randomization. In the OPG group, patients will not be subjected to any other radiographs, whereas in the CBCT group, a CBCT will be done for the mandible in addition to the digital OPG used for screening. This is done to more accurately understand the spatial association between lower wisdom tooth roots and inferior dental canal. The OPG will be assessed for variables such as angulation, depth, difficulty index, length of red line, Rood Shehab’s criteria, as well as type of vertical overlap of third molar root with inferior alveolar canal [11,20].

CBCT images will be evaluated in all three planes. The images will be evaluated to find out the distance from the lower wisdom tooth root to the inferior dental canal and the continuity of the cortical layer between the neurovascular bundle and root. The spatial orientation of the inferior dental canal with regard to the wisdom tooth root will be noted down as either buccal, lingual, inferior, or interradicular. The shape of the IAC at the exact place of contact with the wisdom tooth root will be noted down as oval, round, or narrowed.

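### The plan claims intention-to-treat, but the only analysis set it defines keeps only patients complete on every field, so known primary outcomes would be discarded

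*Protocol article*

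**What the plan says.** The Results section gives the analysis principle: "The statistical analyses will be done with the ‘intention to treat’ principle". The next sentence describes the set to be analysed: "The complete dataset analysis will encompass all study participants, based on the mentioned inclusion/exclusion criteria", and then narrows it to those "who have no missing data for any of the parameters in the dataset". The article names no other analysis set and no method for missing data.

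Three other places bear on how that rule would work:

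- **Table 1 (master chart)** lists the fields of the dataset, including five CBCT columns: canal position, root-to-canal distance, contact, cortical layer and canal shape. Under Patient screening process, the article says "In the OPG group, patients will not be subjected to any other radiographs".
- **Patient screening process** also gives the follow-up schedule: "Patients with altered sensation will be examined at day one, day seven, day 30, day 60, day 90, and then day 180 postoperatively".
- **Participant recruitment** says that the investigators will note the "outcome variables of subjective and objective nerve injury from day one till six months after surgery", without limiting this to patients with symptoms. The Methods part of the Abstract is equally unrestricted.

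**The concern.** Intention-to-treat keeps every randomised patient in the allocated arm. A rule that requires completeness on every parameter removes patients because of what was or was not recorded, much of it after randomisation. The two sentences cannot both govern the primary comparison.

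Three things are at stake:

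- **Known outcomes are thrown away.** The primary outcome is whether a patient reports abnormal sensation. A patient who has answered that question would still be lost over a missing red-line length or alcohol frequency.
- **The rule cannot be applied to this dataset without further choices.** Someone must decide which blank cells count as missing. If that is left until the data are in, the decision may be made with the results in view.
- **The exclusions may depend on the outcome.** If later outcome cells are filled only for symptomatic patients, the rule would drop patients because they were uninjured, and the primary outcome is an incidence.

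**Working it through.** **1. Fields subject to the rule.** Counting the columns of Table 1: 9 demographic + 3 pathological + 7 OPG + 5 CBCT + 7 surgical + 14 outcome = 45. The 14 outcome fields are six subjective, six objective, infection and other complications. Without the CBCT columns, 45 − 5 = 40.

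**2. The plan's own sample size.** Inputs from Sample size calculation: p1 = 0.25 (OPG), p2 = 0.58 (CBCT), 5% significance, 80% power, equal arms (r = 1). The printed formula uses Z(1−α/2).

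- Pooled p = (0.25 + 0.58)/2 = 0.415; √(2 × 0.415 × 0.585) = 0.6968.
- √(0.25 × 0.75 + 0.58 × 0.42) = √0.4311 = 0.6566.
- n = (1.960 × 0.6968 + 0.8416 × 0.6566)² / 0.33² = 3.680/0.1089 = 33.8, so 34 per arm and 68 in total. This matches the plan.

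The text of that section, however, says "Hypotheses will be tested using the one-tailed superiority analysis method". With Z(1−α) = 1.645 the same formula gives 2.886/0.1089 = 26.5, so 27 per arm. Power with 34 per arm is 80% two-sided and 88% one-sided. Both are carried below because the article does not settle which applies. No dropout allowance is stated.

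**3. Literal reading of the rule.** An OPG patient has no CBCT, so all five CBCT fields are blank. If blank means missing, 0 of 34 OPG patients qualify and no between-arm comparison is possible.

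**4. Reading with CBCT fields set aside.** The documents give no missingness rate, so these rates are assumptions. With independent missingness m per field, the share complete on 40 fields is (1 − m)^40.

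| m per field | Share complete | Per arm (of 34) | Power, two-sided | Power, one-sided |
|---|---|---|---|---|
| 0 | 100% | 34 | 80% | 88% |
| 1% | 0.99^40 = 67% | about 23 | 63% | 75% |
| 2% | 0.98^40 = 45% | about 15 | 45% | 58% |

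Independence is pessimistic, because blanks cluster within patients and visits. Stated instead as a total share of patients lost, unrelated to outcome, power is:

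| Patients lost | Two-sided | One-sided |
|---|---|---|
| 5% | 78.1% | 86.7% |
| 10% | 75.8% | 85.0% |
| 20% | 70.6% | 80.9% |
| 30% | 64.5% | 76.0% |

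**5. Selective loss, if it occurs.** Suppose all injured patients are kept and a fraction f of the uninjured. Observed incidence is 0.25/(0.25 + 0.75f) in the OPG arm and 0.58/(0.58 + 0.42f) in the CBCT arm.

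| f | OPG | CBCT | Difference (points) |
|---|---|---|---|
| 1 | 25.0% | 58.0% | 33.0 |
| 0.75 | 30.8% | 64.8% | 34.0 |
| 0.5 | 40.0% | 73.4% | 33.4 |
| 0.25 | 57.1% | 84.7% | 27.5 |
| 0 | 100% | 100% | 0 |

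At f = 0 only about 8.5 OPG and 19.7 CBCT patients remain. Incidence is inflated in both arms from the start. The difference changes little until most uninjured patients are gone, then collapses. The value of f is unknown.

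**The case against.** The strongest reply is that the damaging readings are not what the authors meant.

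- **Loss of the OPG arm.** A reader might infer that the plan deletes its own control group. The documents do not support that as a settled consequence. The CBCT cells are not applicable in that arm, which differs from missing, and the same literalism would drop every man whose oral-contraceptive cell is blank. The article plans a two-group comparison throughout. What stands is that the rule contains no exception for such fields, so it cannot be applied as worded.
- **Selective loss of the uninjured.** A reader might also infer that uninjured patients will certainly be removed. The schedule sentence serves to track recovery and does not say that others go unrecorded. Participant recruitment and the Abstract describe recording to six months without restriction, and the cells are yes/no, so an asymptomatic patient can be entered as N. What stands is that the article leaves this open.
- **The two effects are alternatives.** A set with no OPG patients cannot also show inflated incidence in both arms.
- **A second set.** The complete-dataset analysis might be meant to sit beside an intention-to-treat set. The text does not rule this out, but it does not say so or describe the other set.
- **Power.** The per-field rates are assumed, independence overstates the loss, and under the stated one-tailed test 34 per arm leaves some reserve. All of this is fair, and it is why the figures are illustrations.

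None of it removes the contradiction between the two adjacent sentences, or the loss of known outcomes over unrelated blanks. The absence of a separate analysis plan does not excuse it either, because the article states the rule.

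**Conclusion.** The concern is upheld in a limited form. The intention-to-treat statement and the all-parameters condition contradict each other, and the condition would discard randomised patients with a known primary outcome. That conclusion rests on the text alone and needs no assumption.

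Exclusion of the whole OPG arm follows only if not-applicable cells count as missing. Selective exclusion of uninjured patients follows only if later outcomes are left blank for those without symptoms. Both are possible under the wording, and neither is established.

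The size of the loss is not in the documents. The falls in power to 63% or 45% (two-sided) and 75% or 58% (one-sided) hold only under 1% or 2% independent missingness per field over 40 fields, at the plan's event rates. The case for correction does not depend on them.

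**What to change.** In the Results section:

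1. Delete the condition of completeness on all parameters. Define the primary analysis set as all randomised patients in their allocated arm, regardless of missing covariate or imaging fields.
2. State that fields not applicable by design (CBCT findings in the OPG arm, oral-contraceptive use in men) do not count as missing.
3. Reconcile Participant recruitment with Patient screening process on whose outcomes are recorded at later visits, so that a patient without symptoms is entered as N and not left blank.
4. Say how a missing primary outcome is handled in the main analysis, and add a best-/worst-case sensitivity analysis that keeps every randomised patient in the denominator. Restricting to patients with an observed outcome, without this step, would not be full intention-to-treat.
5. Confine complete-case restriction to the models that need the given covariates, such as the risk-factor logistic regression.

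The cost is a few sentences and one sensitivity analysis. These changes add no patients, visits or measurements, unless reconciling the follow-up text (item 3) shows that patients without symptoms were not going to be asked at later visits.

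### Sensitivity and specificity are planned for OPG and CBCT, but neither image has a defined or recorded positive result, and the protocol article points to two different reference standards

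*Protocol article*

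**What the plan says.** **Accuracy analysis (Results).** "Sensitivity and specificity of CBCT and OPG in prediction of nerve injury will be confirmed on the basis of results obtained". The truth against which both images are judged is described as what is found "on subjective/objective nerve testing after surgical removal of a tooth". The sentence refers the reader to Table 1. The same section says that reporting will follow STARD.

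**Data recorded (Table 1).** There are seven OPG fields: angulation, depth, ramus overlap, difficulty index, red-line length, named Rood-Shehab signs, and class of vertical overlap. There are five CBCT fields: canal position, distance, root contact, cortical layer and canal shape. Root contact and cortical layer are two-valued. No field is labelled a prediction of injury, and none is declared the positive test. Nerve injury is recorded as subjective and as objective, each at six visits.

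**OPG at entry (Patient screening process).** The reader first looks for one or more close-approximation signs. "This will be the eligibility criteria for patient recruitment". Allocation follows: "All these patients will be assigned to either the OPG group or the CBCT group by random computer-generated sequence". Later in the same subsection, without a stated time: "The OPG will be assessed for variables such as angulation, depth, difficulty index, length of red line" and further features.

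**Reference standard.** The subsection headed "Reference standard and its rationale" describes OPG, which it says "is established diagnostic equipment that is used to assess the lower wisdom teeth and their relationship with the inferior dental nerve canal before surgery".

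**Blinding (Training and calibration of personnel).** Image readers are blinded to the clinical outcome.

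**The concern.** Sensitivity and specificity are defined only once each image yields a positive or negative call and one outcome is named as the truth. The article supplies neither. It lists features, and someone must later decide which feature, at which cut-off, means that injury was predicted. It also leaves open which of several nerve-testing results that call is compared with.

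Prediction of nerve injury is the stated aim, and the Discussion promises a comparison of diagnostic accuracy. If the rule is settled with the outcomes in hand, in a group as small as 34, an image that carries no information can appear to predict injury. Placing OPG under the reference-standard heading adds a contradiction: in a STARD report, OPG cannot be both a test under evaluation and the standard it is evaluated against.

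**Working it through.** **1. The plan's own figure.** The article states no accuracy figure. The number needed here is the arm size, which reproduces from the printed formula with p1 = 0.25, p2 = 0.58, r = 1, Z(1-α/2) = 1.960 and Z(1-β) = 0.842:

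- pooled p = (0.25 + 0.58)/2 = 0.415
- first term: 1.960 × √(2 × 0.415 × 0.585) = 1.366
- second term: 0.842 × √(0.25 × 0.75 + 0.58 × 0.42) = 0.553
- n = (1.366 + 0.553)² / 0.33² = 33.8, so 34 per arm and 68 in total

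The trial is therefore sized on the incidence of abnormal sensation, not on accuracy. At the article's rates, 34 × 0.25 = 8.5 (8 used below) injuries are expected in the OPG arm and 34 × 0.58 = 19.7 (20 used below) in the CBCT arm.

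**2. The only OPG rule in the text.** Take at least one close-approximation sign as OPG-positive. Every enrolled patient has such a sign, so there are no OPG-negatives:

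| Arm | Injured, OPG+ | Injured, OPG− | Uninjured, OPG+ | Uninjured, OPG− | Sensitivity | Specificity |
|---|---|---|---|---|---|---|
| OPG | 8 | 0 | 26 | 0 | 8/8 = 100% | 0/26 = 0% |
| CBCT | 20 | 0 | 14 | 0 | 20/20 = 100% | 0/14 = 0% |

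This holds whatever the injury rate. OPG needs another rule, and none is given.

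**3. Choices left open for the truth.** 2 outcome types × 6 visits = 12 candidate columns in Table 1, with none selected.

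**4. What an open CBCT rule could do (illustration, not a forecast).** Take 34 patients and five CBCT features unrelated to injury. Candidate calls: position 4 (each level against the rest) + distance 7 (quantile cut-offs) + contact 1 + cortical layer 1 + shape 3 = 16. The level frequencies, the seven cut-offs and the list of calls are assumptions, since the article gives none of them. Keep the call with the highest Youden index (sensitivity + specificity − 1), whose true value is 0. The ranges span different assumed frequencies, including a variant that lets a call run in either direction.

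| Search | Mean best apparent Youden index | At least one p < 0.05 |
|---|---|---|
| 16 calls | about 0.26 to 0.36 | 26% to 33% |
| Two binary fields only, fixed direction | 0.10 to 0.11 | 5% to 7% |
| One call fixed in advance | 0.00 to 0.01 | not reported |

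As a separate check, tuning the cut-off of a single uninformative continuous marker in 34 patients gives a mean apparent index of 0.22 with 8 injuries and 0.19 with 20. These figures vary only the image rule. Choosing among the 12 outcome columns would add further freedom and is not included.

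**5. Precision even with a fixed rule.** With 20 injuries, an observed sensitivity of 16/20 has an exact 95% interval of 0.56 to 0.94. With 8 injuries, 6/8 has 0.35 to 0.97. Intervals this wide leave little to contradict an optimistic cut-off.

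**The case against.** The strongest reply is that a condensed article may leave the positivity rule to a full protocol or analysis plan that is not shown. Two CBCT fields are already binary, so a rule could be fixed before unblinding with no new column. That stands in part: the rule may exist elsewhere. But the article prints its data form, and that form has no prediction. A later document can define a rule from recorded features; it cannot recover a reader's risk call that was never written down before surgery.

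Readers are blinded to outcome. This protects the recorded features. It does not protect the later choice of which feature counts as positive.

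The reference-standard heading may be only a labelling slip. The Results section plainly makes nerve testing the truth, and no planned analysis uses OPG as truth. That is fair, and the repair is to the wording. The choice of outcome and visit remains open all the same.

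The 16-call search is not something the article plans, and its size depends on assumed inputs. This stands, and it is why the result is given as a worst case beside the much smaller figure for the two binary fields.

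Two stronger readings are tempting, and the text does not support them. A reader might infer that OPG is read only after allocation, perhaps with the CBCT in view. In fact the eligibility reading precedes allocation, and for the remaining OPG variables the timing is simply not stated. A reader might also infer that the cut-off will be chosen once outcomes are known. No sentence says so; the plan permits it but does not declare it.

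**Conclusion.** The concern holds in a limited form. As written, sensitivity and specificity are undefined for both images, and no pre-operative prediction is recorded. The only OPG rule in the text gives 100% and 0% by design, which follows from the entry criterion and needs no assumption. The article also contradicts itself on the reference standard and leaves 12 candidate truth columns open.

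The possible inflation is less certain. It ranges from about 0.1 on the Youden scale, if the choice lies between the two binary CBCT fields, to about 0.26 to 0.36 for an exhaustive search, under assumed feature frequencies and features that carry no information.

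The incidence-based primary comparison and its sample size are untouched. How far the CBCT referral protocol (third objective) would lean on these accuracy figures is not stated; the Discussion also mentions correlating imaging findings with outcomes and identifying risk factors. This should be corrected because the calls cannot be collected retrospectively and the correction is cheap.

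**What to change.** 1. Add two columns to Table 1: an OPG high/low injury-risk call made on the screening OPG and locked before allocation in every patient, and a CBCT high/low injury-risk call locked before surgery in the CBCT arm.
2. State in the Results section that these two calls are the index tests for sensitivity and specificity, that the entry sign is not the OPG-positive rule, and that any cut-off built from individual features is exploratory.
3. Under the reference-standard heading, describe OPG as the comparator index test, and name one post-operative nerve-injury result at one visit from Table 1 as the reference standard.

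Cost: two more chart entries per CBCT patient and one per OPG patient, recording the OPG call at screening, and a few changed sentences. No imaging is added. The accuracy reported may look lower than with a tuned cut-off.
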